## Abstract

**Background:**

Chronic obstructive pulmonary disease (COPD) contributes significantly to mortality, hospitalisations and health care costs worldwide. There is evidence that the detection, accurate diagnosis and management of COPD are currently suboptimal in primary care. Physiotherapists are well-trained in cardiorespiratory management and chronic care but are currently underutilised in primary care. A cardiorespiratory physiotherapist working in partnership with general practitioners (GPs) has the potential to improve quality of care for people with COPD.

**Methods:**

A prospective pilot study will test the feasibility of an integrated model of care between GPs and physiotherapists to improve the diagnosis and management of people with COPD in primary care. Four general practices will be selected to work in partnership with four physiotherapists from their local health district. Patients at risk of developing COPD or those with a current diagnosis of COPD will be invited to attend a baseline assessment with the physiotherapist, including pre- and post-bronchodilator spirometry to identify new cases of COPD or confirm a current diagnosis and stage of COPD. The intervention for those with COPD will involve the physiotherapist and GP working in partnership to develop and implement a care plan involving the following tailored to patient need: referral to pulmonary rehabilitation (PR), physical activity counselling, medication review, smoking cessation, review of inhaler technique and education. Process outcomes will include the number of people invited and reviewed at the practice, the proportion with a new diagnosis of COPD, the number of patients eligible and referred to PR and the number who attended PR. Patient outcomes will include changes in symptoms, physical activity levels, smoking status and self-reported exacerbations.

**Discussion:**

If feasible, we will test the integration of physiotherapists within the primary care setting in a cluster randomised controlled trial. If the model improves health outcomes for the growing numbers of people with COPD, then it may provide a GP-physiotherapist model of care that could be tested for other chronic conditions.

**Trial registration:**

ANZCTR, ACTRN12619001127190. Registered on 12 August 2019—retrospectively registered.

## Background

Chronic obstructive pulmonary disease (COPD) contributes significantly to mortality, hospitalisations and health care costs worldwide [1]. In Australia alone, COPD contributed to 4.5% of all deaths [2] and was the principal diagnosis for 66,540 hospitalisations for people aged 45 and over in 2015 [3]. COPD is the 11th most commonly managed chronic condition in Australian general practice [4]. The COPD-X Concise Guide for Primary Care identifies general practice as an ideal setting for the diagnosis and management of COPD [5]; however, despite best available evidence-based recommendations, COPD remains under-diagnosed, misdiagnosed and management has been suboptimal in primary care. For example, the Burden of Obstructive Lung Disease Survey found that the prevalence of airflow limitation (GOLD stage II or higher) in Australians 40 years and over was 7.5%, whereas the prevalence of doctor-diagnosed COPD in the same population was only 5.2% [6].

High-quality spirometry testing is one way to improve the diagnosis of COPD in primary care [5, 7] yet evidence indicates that the use of spirometry in general practice is low [8–10]. There are multiple factors contributing to the suboptimal use of spirometry in primary care. Firstly, GPs are not adequately reimbursed by Medicare to undertake pre- and post-bronchodilator spirometry with current reimbursement being only $34.95 from the Medicare Benefits Schedule which can only be claimed once in any 12-month period. A further barrier is that some GPs and practice nurses (PNs) lack confidence in the interpretation of spirometry [11] with one study reporting that GPs and PNs misinterpreted spirometry in 30% of cases [12].

Improvement in the diagnosis of COPD could be achieved through case-finding methods. This involves the identification of ‘high-risk patients’ and utilising standardised screening questionnaires in addition to spirometry. Previous studies have targeted people over the age of 40 years who are current or ex-smokers with a 10-year or more pack history and have focused on upskilling GPs, PNs or research assistants at performing these screening techniques. These methods have been shown to be effective with the identification of new cases of COPD ranging from 4 to 27%, as well as identifying a high rate of misdiagnosis [12–14].

Once COPD has been confirmed and pharmacological management optimised, one of the most effective non-pharmacological interventions for individuals with COPD is pulmonary rehabilitation (PR). PR has been shown to lead to improvements in exercise tolerance, dyspnoea, depression and overall health-related quality of life [15–18]. However, despite strong international recommendations, referral to PR from healthcare professionals is low. It is estimated that only 3–16% of eligible patients are referred to PR and even fewer people (1–2%) actually receive this intervention [16, 19]. In particular, referral rates from primary care are low with one study reporting only 5% of eligible patients were referred to PR by general practitioners [20]. The barriers to referral and attendance at PR are well known. These include low awareness and knowledge of PR and the benefits of PR, low knowledge of the referral process and a lack of persuasive health professional communication [21–23]. Current guidelines also recommend the use of multidisciplinary care plans in the management of patients with COPD [5]. Multidisciplinary care plans, initiated by GPs, anticipate the wide range of long-term needs of patients with COPD and have been found to improve exercise capacity and health-related quality of life and reduce hospitalisation [24–26]. However, some studies have found that GPs need more support to develop and implement multidisciplinary care plans in some chronic conditions such as asthma [27, 28].

The issues surrounding the management of COPD in primary care are complex, and there is a need for alternative strategies to improve outcomes for patients with COPD. Zwar et al. (2016) tested a GP-nurse partnership approach in the management of newly diagnosed COPD and found no difference in outcomes compared to usual care [12]. Furthermore, they found that some PNs still lacked confidence in the diagnosis and management of COPD despite additional training [11]. One alternative method could be to utilise multi-component inter-disciplinary management which, in a COPD population, has shown improvements in some patient outcomes including disease-specific quality of life [29, 30], patient self-reported physical activity levels [31] and exercise capacity [30]. A Cochrane review has reported a reduction in hospital admissions and hospital days per person in favour of the inter-disciplinary management approach [30].

Physiotherapists play an important role in respiratory disease management in Australian hospitals, particularly in coordinating PR programmes and in providing physical activity advice. Physiotherapy students in Australia undertake extensive training in cardiopulmonary physiotherapy. This training includes the use and interpretation of spirometry, conducting exercise testing for people with respiratory disease and exercise prescription within a PR programme. Physiotherapists are, therefore, well positioned to work in partnership with GPs to better manage patients with chronic lung disease but are currently underused in this role in primary care. Physiotherapy services, as a first point of contact, have been shown to be safe, effective and well received by patients with musculoskeletal complaints [32, 33]. There is currently no published literature on a GP-physiotherapist partnership model in primary care in an Australian setting to improve identification and management of COPD.

## Study aims and hypothesis

The primary aim of the INTEGRATED study (InNovaTivE Gp-physiotheRapist pArTnErship for copD) is to determine the feasibility and acceptability of this integrated model of GP and physiotherapist partnership. The secondary aims are to (1) produce high-quality spirometry with accurate interpretation to both identify new cases of COPD and determine the stage of severity for known cases of COPD, (2) increase general practice referrals to pulmonary rehabilitation for people that meet the COPD-X guidelines criteria for referral [5], (3) increase physical activity levels in people with COPD at 3 months compared to baseline and (4) increase smoking cessation in those who are smokers at baseline.

The INTEGRATED study hypothesises that a GP and physiotherapist model of care will be a feasible and acceptable way to improve the diagnosis and management of people with COPD. This will be achieved through more accurate spirometry interpretation, at least 90% of participants who meet the COPD-X guidelines for referral to PR being referred to a programme, an increase in physical activity levels by participants at 3 months compared to baseline, and at least 50–75% of participants have attended or commenced a smoking cessation programme at 3 months after their baseline visit.

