#### New cases of COPD

The physiotherapist will initiate and work in partnership with the GP and patient to develop a COPD specific GP Management Plan (GPMP) and where necessary, Team Care Arrangement (TCA) [43] for the participant using the template developed from the PELICAN Study [44]. This is necessary in Australia to access Medicare subsidised management by an allied health provider such as a physiotherapist. The problems identified in the assessment and the plan of action including details of specific management will be documented. If necessary, patients will also be referred back to the GP for review and medical management as required. Patients will receive physical activity advice and counselling using the 5 A’s approach (Ask, Advise, Assess, Assist, Arrange follow-up) according to the Australian Physical Activity and Sedentary Behaviour Guidelines [45] and a pedometer to monitor their physical activity goals and guide exercise prescription at follow-up appointments. The 5As are a clinical tool recommended for health behaviour counselling in primary care which will enable the physiotherapist to identify barriers to engaging in regular physical activity as well as strategies to overcome these barriers and tailor physical activity goals towards the participant. Patients will also be referred to PR if they meet the requirement according to the COPD-X guidelines [5]. These guidelines state that all patients with COPD (of all mMRC grades) will benefit from PR and recommend that all patients with exertional dyspnoea, those at risk of exacerbation and following an exacerbation should be referred to PR [5]. All current smokers will receive individualised smoking cessation advice and support and appropriate referrals will be made back to the GP as informed by the Royal Australian College of General Practitioners (RACGP) guidelines [46]. Participant education booklets regarding physical activity guidelines, smoking cessation and COPD management will also be provided.

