#### Primary outcomes

##### Feasibility outcomes

A summary of the outcomes that will be used to determine the feasibility of this health service model on the effective identification and management of COPD can be found in Table 1. The primary outcome measures will be number (%) identified with obstruction from the case-finding cohort and number (%) eligible and referred to PR programmes. The success target for number (%) identified with obstruction will be set at 15% as previous studies have reported rates of case finding new diagnoses of COPD between 4 and 27% [12–14]. International literature suggests that only 5% of eligible patients are referred by GPs to PR [20]. We would determine the clinics successful if 80% of eligible participants are referred to PR by the clinics and at least 50% of those referred attend an appointment.

**Table 1 Tab1:** Summary of process outcomes to determine feasibility

Existing COPD	New cases of COPD
Number (%) with spirometry completed (FEV_1_ and FVC data) meeting ERS/ATS quality criteria	Number (%) with spirometry completed (FEV_1_ and FVC data) meeting ERS/ATS quality criteria
Number of known COPD patients over 40 years in the general practice	Number of smokers/ex-smokers over 40 years in the general practice
Number (%) invited to attend	Number (%) invited to attend
Number (%) attended first appointment with physiotherapist	Number (%) attended first appointment with physiotherapist
Number (%) confirmed diagnosis and severity	Number (%) confirmed diagnosis and severity
Number (%) eligible for PR	Number (%) eligible for PR
Number (%) referred to PR	Number (%) referred to PR
Number (%) attended PR	Number (%) attended PR

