##### Sample size and feasibility

We will recruit a minimum of four general practices to the study. Based on data from a previous study [48], it is anticipated that each practice will identify 104 potentially eligible patients with a diagnosis of COPD with 50% participation and 52 patients are likely to consent to take part in the study. It is estimated that the four practices will identify a total of 1060 patients who are at risk of COPD but without a current diagnosis. Of these, 17% (180) will attend for spirometry and assessment and 18% [33] will receive a new diagnosis of COPD [12].

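### The target for referring eligible participants to pulmonary rehabilitation is 90% in the hypothesis and 80% in the primary feasibility outcomes, and the article does not say how the two relate

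*Protocol article*

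**What the plan says.** Three statements in the protocol article bear on this.

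- **Study aims and hypothesis, the hypothesis.** The model is expected to be a feasible and acceptable way to improve diagnosis and management. The next sentence opens "This will be achieved through more accurate spirometry interpretation" and goes on to list "at least 90% of participants who meet the COPD-X guidelines for referral to PR being referred to a programme".
- **Study aims and hypothesis, the aims.** Feasibility and acceptability form the primary aim. The second of the secondary aims is to "increase general practice referrals to pulmonary rehabilitation for people that meet the COPD-X guidelines criteria for referral".
- **Primary outcomes, Feasibility outcomes.** "The primary outcome measures will be number (%) identified with obstruction from the case-finding cohort and number (%) eligible and referred to PR programmes". The success rule follows: "We would determine the clinics successful if 80% of eligible participants are referred to PR by the clinics", with the further condition that "at least 50% of those referred attend an appointment".

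The Statistical analysis section plans descriptive analysis only for the process outcomes. The abstract and the closing discussion make a later randomised trial conditional on the model proving feasible.

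**The concern.** Two numerical marks are set for what appears to be one proportion, and it is one of only two named primary outcome measures. No formal test is planned on it, so the mark stated in advance is the main safeguard on how the result is interpreted. If two marks stand, a result between them can be reported as meeting the referral criterion or as falling short of the hypothesis, and the choice can be made after the rate is known. The status of referral is also unsettled, since it is a secondary aim in one section and a primary outcome measure in another. A reader therefore cannot tell from that labelling which section should take precedence.

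**Working it through.** **Step 1. Is it the same quantity?**

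| | Hypothesis | Feasibility outcomes |
|---|---|---|
| Numerator | participants referred to PR | participants referred to PR |
| Denominator | those meeting COPD-X referral criteria | eligible participants |
| Mark | at least 90% | 80% |
| Further condition | none on attendance | at least 50% of those referred attend |
| Status of referral | secondary aim | primary outcome measure |

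The two denominators are worded differently, but COPD-X is the only eligibility standard for referral in the article. The intervention section for new cases says "Patients will also be referred to PR if they meet the requirement according to the COPD-X guidelines", and the section on existing COPD uses the same standard. No different population, time point or referrer is given that would explain two figures.

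**Step 2. How many patients could be involved?** The section on sample size and feasibility states that "each practice will identify 104 potentially eligible patients with a diagnosis of COPD with 50% participation and 52 patients are likely to consent". Reproducing its figures:

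- Existing COPD: 104 × 0.50 = 52 per practice, and 52 × 4 = 208.
- At-risk attenders: 1060 × 0.17 = 180.2, stated as 180.
- New diagnoses: 180 × 0.18 = 32.4. The text shows 33 in brackets, which I read as a count.
- Total with COPD: 208 + 33 = 241, if every consenting patient with recorded COPD is confirmed on spirometry.

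The share eligible for PR is not stated, so the number eligible, n, is an assumption. I use 150 to 240 as the main range and n = 60 (about 25% of 241) as a low case.

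**Step 3. Which results conflict?** These are the counts of at least 0.80n but below 0.90n.

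- n = 150: 120 to 134 referred
- n = 180: 144 to 161
- n = 240: 192 to 215
- n = 60: 48 to 53

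**Step 4. How likely is such a result?** With X ~ Binomial(n, p), where p is the true referral rate:

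P(conflict) = P(X ≥ 0.80n) − P(X ≥ 0.90n)

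At p = 0.85:

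- n = 150: 0.962 − 0.049 = 0.913
- n = 180: 0.973 − 0.033 = 0.940
- n = 240: 0.986 − 0.015 = 0.970 (unrounded tails)

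Across true rates:

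| True rate | n = 150 | n = 180 | n = 240 | n = 60 |
|---|---|---|---|---|
| 70% | 0.4% | 0.2% | <0.1% | 5.7% |
| 75% | 9.1% | 6.9% | 4.1% | 22.8% |
| 80% | 54.8% | 54.4% | 53.9% | 54.6% |
| 85% | 91.3% | 94.0% | 97.0% | 70.9% |
| 90% | 43.2% | 43.8% | 44.6% | 38.8% |
| 95% | 0.4% | 0.2% | <0.1% | 3.0% |

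These probabilities concern the referral rate only. They do not include the attendance condition, for which the article gives no expected rate. They also treat patients as independent, although referral is made through four practices.

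**The case against.** The strongest reply is that the two figures do different jobs. Only the feasibility outcomes section speaks of a success target and of judging the clinics successful, whereas the hypothesis says what the authors expect. An expectation of 90% with a minimum acceptable 80% would be coherent. This has weight, and it is why the 80% statement is the natural one to keep. But the article does not draw the distinction. The 90% is worded as a minimum, and the text presents it as one of the means by which the feasibility hypothesis is met.

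Several stronger readings are tempting, and the article does not support them.

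- **That any rate in the 80-90% band is a success under the outcome section.** It is not, because the rule also needs at least 50% of those referred to attend. Such a rate meets the referral half only.
- **That such a rate would reject the hypothesis.** Nothing is tested against 90%. The analysis is descriptive, and the hypothesis is a composite that also covers spirometry interpretation, physical activity and smoking cessation.
- **That the later trial turns mechanically on this number.** The article says only that it follows if the model is feasible, and acceptability interviews also inform that judgement.
- **That the verdict almost always depends on the section read.** That is so near a true rate of 85%, the middle of the disputed band. Well outside the band the two marks seldom disagree.
- **That retrospective registration shows a threshold would be picked after the fact.** It does not, and it is a separate matter.

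It is also fair to say that both marks lie far above the 5% referral rate the article cites for general practice. A result in the band would be a large improvement on that figure under either reading.

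**Conclusion.** The point holds: the referral target is wrong as written. One proportion carries two marks, 90% and 80%, and two levels of importance, secondary aim and primary outcome measure, with no statement connecting them. A result from 80% to just under 90% would leave the referral part of the feasibility verdict open to either reading.

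How likely that is depends on the true rate. It is near certain around 85%, roughly an even chance at 80% or 90%, and small at 75% or below and at 95% when 150 to 240 patients are eligible. With only 60 eligible the band is still hit 71% of the time at 85%, and the chance is larger than in the main range at 70%, 75% and 95%. The contradiction itself is textual and rests on none of these assumptions. Only its size depends on the assumed number eligible, the assumed true rate and independence between patients.

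**What to change.** Before referral data are summarised, reconcile the two sections to one referral criterion. The feasibility outcomes section holds the only explicit success rule: 80% of eligible participants referred, together with at least 50% of those referred attending. Two wordings would work:

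- change the hypothesis so that it states that rule; or
- keep 90% in the hypothesis, labelled as an expectation that does not decide feasibility.

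State in the same edit whether referral counts as a primary outcome or a secondary aim. The cost is one sentence of wording, with no change to recruitment, data collection or analysis.

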#### New cases of COPD

Patients will be eligible if they have attended the practice at least twice with one visit in the preceding 12 months, are aged 40 years or over and have a documented history of smoking (current or former smoker) in their medical notes. A history of current smoking or past smoking will identify those patients who are at high risk of developing COPD.

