#### Existing COPD

Patients will be eligible if they are aged 40 years or over, have a recorded diagnosis of COPD or are taking medications prescribed for COPD (such as short-acting inhaled β_2_ agonists (SABA), short-acting muscarinic antagonists (SAMA), long-acting inhaled β_2_ agonists (LABA), long-acting muscarinic antagonists (LAMA), combination of LABA/LAMA and inhaled corticosteroids), and they have visited the practice in the last 12 months.

Patients will be excluded if they have terminal cancer, cognitive impairment, require home oxygen, do not speak sufficient English or are pregnant.

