##### Secondary outcomes

The secondary outcome measures are summarised in Table 2 and consist of the patient-relevant outcomes. Health status and symptom score will be measured by the CAT. The CAT has been shown to be a validated tool in the assessment of disease-related quality of life [37] with the most reliable estimate of the minimum important difference being a change of 2 points [47]. Dyspnoea will be assessed using the mMRC [38] which is rated on a scale of 0 (‘I only get breathless with strenuous exercise’) to 4 (‘I am too breathless to leave the house’ or ‘I am breathless when dressing or undressing’).

**Table 2 Tab2:** Summary of patient outcomes

Existing COPD	New cases of COPD
Symptom Score (CAT)	Symptom Score (CAT)
Meeting physical activity guidelines (Y/N) self-reported using AAQ	Meeting physical activity guidelines (Y/N) self-reported using AAQ
COPD Diagnostic Questionnaire (CDQ) score	COPD Diagnostic Questionnaire (CDQ) score
Dyspnoea score (mMRC)	Dyspnoea score (mMRC)
Patient Activation Measure (PAM)	Patient Activation Measure (PAM)
Daily step count (pedometer)	Daily step count (pedometer)
Smoking status	Smoking status
Self-reported exacerbations	Self-reported exacerbations
Self-reported hospital admission	Self-reported hospital admission
Self-reported emergency attendance	Self-reported emergency attendance

Physical activity will be measured in two ways. The first method will be self-reported activity levels and whether they are meeting the Australian Physical Activity and Sedentary Behaviour Guidelines [45] determined by the AAQ. The second method is the recording of daily steps from a pedometer which will be worn either around the patient’s neck or in their pocket. To assist the physiotherapist in exercise prescription, the PASOCQ [41] will also be used to determine the participant’s readiness for change. This questionnaire consists of 4 questions which places participant’s into one of the five stages of change (pre-contemplation, contemplation, preparation, action and maintenance phases).

Patient health activation will be assessed using the PAM [40] which is a 22-item measure that assesses patient knowledge, skill and confidence for self-management.

Hospital utilisation will be assessed through self-report of exacerbations, hospital admissions and emergency department attendance.

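### The smoking-cessation target in the secondary hypothesis gives a range where one threshold is needed, counts all participants rather than baseline smokers, and measures something different from aim 4 and the listed outcomes

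*Protocol article*

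**What the plan says.** Under Study aims and hypothesis, the fourth secondary aim is to "increase smoking cessation in those who are smokers at baseline". The next paragraph turns the aims into expected results, and for smoking it expects that "at least 50–75% of participants have attended or commenced a smoking cessation programme at 3 months after their baseline visit". The target for pulmonary rehabilitation (PR) in the same sentence is "at least 90% of participants who meet the COPD-X guidelines for referral to PR being referred to a programme", which has a single figure and a restricted denominator.

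Eligibility does not limit the cohort to current smokers. Case-finding patients must "have a documented history of smoking (current or former smoker) in their medical notes". Existing-COPD patients must "have a recorded diagnosis of COPD or are taking medications prescribed for COPD", with no smoking criterion. In the intervention section for new cases, cessation support is for smokers: "All current smokers will receive individualised smoking cessation advice and support and appropriate referrals will be made back to the GP". The existing-COPD section gives it where applicable, and the section on those without COPD again limits it to current smokers.

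Table 1 (process outcomes) has rows for PR eligibility, referral and attendance, and none on smoking. The only smoking entry in Table 2 (patient outcomes) is "Smoking status". The numerical success criteria under Feasibility outcomes concern obstruction found (15%), PR referral (80%) and PR attendance (50%).

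**The concern.** A target is useful if a result can be held against it and declared met or not met. That needs one figure, a denominator made up of people who could have the event, and a measure that records the event. The smoking target is unclear on the first, wrong on the second if taken at its word, and not matched to a listed measure on the third.

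At stake is one of four components through which the hypothesis is to be achieved. If the bound and the denominator are settled only once the data are in, the same result can be reported as success or as failure. If attendance is not collected, smoking status cannot replace it, since a person can enter a programme without quitting or quit without entering one.

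**Working it through.** **Inputs.** From Sample size and feasibility: 104 eligible existing-COPD patients per practice with 50% participation; four practices; 1060 at-risk patients, of whom 17% attend and 18% of attenders are newly diagnosed. From Study aims and hypothesis: the 50–75% range. The document gives no current-smoker share, so the shares below are assumptions.

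**The plan's own figures.** 104 × 0.50 = 52 per practice, as printed. 1060 × 0.17 = 180.2, printed as 180. 180 × 0.18 = 32.4; the text prints 33 in square brackets, which I take as the count. The smoking target has no derivation to reproduce.

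**Cohort followed to 3 months.** Only people with existing or newly diagnosed COPD return, so the expected number is 4 × 52 + 33 = 241.

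**Denominator.** With all 241 counted, the lower bound needs 0.50 × 241 = 120.5, so 121 people in a programme. The upper bound needs 0.75 × 241 = 180.75, so 181. If only current smokers can enter a programme, the maximum share of all participants is the current-smoker share s, and the uptake among smokers needed is 0.50/s or 0.75/s. A value above 1 is impossible.

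| Assumed s | Smokers of 241 | Ceiling, % of all | Uptake needed for 50% | Uptake needed for 75% |
|---|---|---|---|---|
| 20% | 48 | 19.9 | 2.50 | 3.75 |
| 30% | 72 | 29.9 | 1.67 | 2.50 |
| 40% | 96 | 39.8 | 1.25 | 1.88 |
| 50% | 120 | 49.8 | 1.00 | 1.50 |
| 60% | 145 | 60.2 | 0.83 | 1.25 |
| 75% | 181 | 75.1 | 0.67 | 1.00 |

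Ceilings differ slightly from s because smokers are rounded to whole people. If attenders without COPD also count as participants, the total is 208 + 180 = 388 and the bounds become 194 and 291. The ceilings are the same within rounding, but those without COPD have no scheduled 3-month contact.

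**Threshold.** Now take baseline smokers as the denominator. With 72 smokers (s = 30%), the bounds are 36 and 54, and both are attainable. Counts from 36 to 53 meet one bound and miss the other. The binomial chance of meeting each bound at a true uptake of 60% is:

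| Smokers | Meets 50% | Meets 75% |
|---|---|---|
| 48 | 0.940 | 0.022 |
| 72 | 0.967 | 0.006 |
| 96 | 0.982 | 0.001 |

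At this uptake, the choice of bound decides the verdict.

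**Event.** The aim concerns quitting among baseline smokers, the hypothesis concerns attending or starting a programme, and Table 2 lists smoking status. The listed measure fits the aim but not the hypothesis. For PR, by contrast, the hypothesis is about referral and Table 1 has a referral row.

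**The case against.** The best reply is that the intention can be recovered. The aim just before the hypothesis is limited to baseline smokers, and the intervention sections direct cessation support to current smokers, so a sensible reader would supply that denominator. On that reading both bounds can be reached. The range can also be read as a floor of 50% with 75% as an aspiration. This is probably close to what was meant, but the text says neither, and the neighbouring PR target shows that the hypothesis does restrict a denominator where it wants to.

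A reader might go further than the documents allow in four ways:

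- **That the target is unattainable.** This depends on a smoker share that is not given. At 60% or more the lower bound comes within reach even on the literal reading, and nothing in the eligibility criteria excludes such a share.
- **That the hypothesis cannot be tested.** Among smokers, results below 50% or at 75% and above are clear on either reading. Only the band between is undefined.
- **That programme attendance is not collected.** Both tables are titled as summaries, the data collection figure is not shown, and the case report forms are not at hand. The article supports only that attendance is not listed.
- **That the feasibility verdict is compromised.** The stated success criteria do not mention smoking, and no progression decision is tied to the range.

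**Conclusion.** The point holds as a misstated target for one secondary hypothesis. Three things are established from the text alone: the range has no governing bound, the denominator conflicts with the aim it serves, and the event differs from both the aim and the listed smoking measure.

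The size of the denominator problem is conditional. Assuming that only current smokers enter a cessation programme, the literal target cannot meet its lower bound when fewer than half of participants smoke, nor its upper bound when fewer than three quarters do. The effect of the range does not depend on the denominator error: with 72 smokers (an assumed 30% of 241) and 60% true uptake, success has probability about 0.97 against one bound and 0.006 against the other.

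The consequence is confined to aim 4 and its part of the hypothesis. Aim 4 itself remains measurable, because smoking status is listed and a 3-month assessment is scheduled. It should be corrected, but it does not threaten the study's main conclusions.

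**What to change.** Make three changes:

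1. In the hypothesis, state one threshold of the sponsor's choosing, with participants with COPD who are current smokers at baseline as the denominator.
2. Add an outcome to Table 1: the number and percentage of baseline smokers who have entered a cessation programme by 3 months.
3. For aim 4, report smoking status at 3 months among baseline smokers as a separate result.

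The cost is a wording change and, if attendance is not already recorded, one question at the existing 3-month visit or its telephone substitute. Recruitment began in October 2018, so the change should be dated and labelled as made during the study. Attendance may also be missing for participants already past their 3-month contact, and the report should state how many.
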